#### Physical activity

The intervention will comprise 6 weekly small-group sessions. The purpose of these sessions will be to educate patients about the interaction of physical activity, mood and diabetes, and to increase their participation in a variety of physical activities with an emphasis on walking. The sessions will combine interactive lectures and exercise techniques (warm-up, flexibility, strengthening and stretching exercises) that are considered suitable for the study participants. The educational topics will include effects of exercise on mood; short- and long-term effects of exercise on blood glucose and the cardiovascular system; and strategies to develop and maintain a personal plan for regular exercise. The programme has been developed by a professional trainer experienced in working with the diabetic population.

The sessions will be organised in a group format and led by a professional trainer. Exercise intensity will be measured by a heart rate monitor and maintained in a light-to-medium intensity range. The volume of physical activity will be monitored by a pedometer for one week preceding each point of measurement.

#### Depression screening followed by diabetes treatment as usual

The patients screened for depression will be given an explanation of their results and informed about the importance of treating depression, as well as about different treatment options. They will be provided with brief re-education on diabetes aimed at alleviating diabetes-related burden, and with written self-help instructions to cope with mood difficulties.

Follow-up data will be collected at the same points of measurement as in the treatment groups.

### Assessments

Patients will be assessed at four time points: at baseline (T0), at the end of the interventions (i.e., 6 weeks after the beginning, T1), at 6 months (T2) and at 12 months (T3) after the beginning of the intervention (Figure 2). Data will be collected by experienced researchers blinded to group assignment.

**Figure 2 F2:**
[figure not shown]
**Study flowchart**.

Data concerning the patients' psychological history (psychological morbidity, treatment method, symptom course, family history of psychiatric morbidity) and current psychosocial situation (family and professional status, economic circumstances, recent stress experiences, perceived social support) will be collected at baseline by semi-structured telephone interview.

Psychological questionnaires will be applied at all points of measurement to collect data on patients' emotional state and their experience in living with diabetes: depressive symptoms (Center for Epidemiologic Studies Depression Scale, CES-D), diabetes distress (Problem Areas in Diabetes, PAID), health-related quality of life (Short Form Survey, SF-12) and diabetes self-care (Summary of Diabetes Self-Care Activities, SDSCA). The questionnaires have been psychometrically evaluated in Croatian diabetic patients. SCID-I will be re-administered after 12 months.

To assess the level of physical activity, a subscale of the Summary of Diabetes Self-Care Activities (SDSCA) referring to the frequency and intensity of physical activity during previous week will be applied at all measurement points. To provide objective data, patients from both the intervention groups and the control group will wear the pedometer for one week preceding all points of measurement, including the baseline.

Baseline information on the type, duration and treatment of diabetes, body mass index (BMI), waist-to-hip ratio (WHR), and concomitant somatic diseases will be retrieved from the patients' medical records. If necessary, an internist will be consulted about the interpretation of data. Biochemical parameters including HbA_1c_, lipids, and albumin/creatinine ratio, and data on patients' body weight, blood pressure and diabetes medication will be determined and recorded at all points of measurement. Fasting plasma glucose and insulin will be used to assess insulin resistance by a HOMA-2IR model [38]. Low-grade inflammation will be monitored by high sensitivity C-reactive protein, total sialic acid [39], WBC and neutrophil counts. Urinary 8-hydroxy-2'-deoxyguanosine and serum malondialdehyde and 4-hydroxyalkenals will be used as biomarkers of DNA and lipid oxidative damage, respectively, whereas uric acid as the most prominent low-molecular weight endogenous antioxidant will be measured by an automated enzymatic technique at T0, T2 and T3, to avoid possible short-term biological interferences of exercise.

Patients will provide their self-monitoring blood glucose (SMBG) records kept in accordance with their treatment algorithms and recommendations over the whole study period.

Due to a possible interaction between depression and neuropathic pain, patient self-assessments of neuropathic pain will be evaluated by a simple visual analogue scale at all points of measurement.

Indicators of glycaemic control (HbA_1c_) will be determined by an automated immunoturbidimetric method using commercially available reagents (Roche Diagnostics), traceable to the NGSP/DCCT standard, with a total imprecision (CV) of 2.8%.

Patients' preferences regarding the type of treatment (psychoeducation, physical activity intervention, treatment as usual) will be recorded. Although it is assumed that this might influence drop out, adherence and intervention impact, the methodological benefits of randomisation outweigh the potential costs. Possible effects of treatment preference on outcome measures will be controlled for statistically.

### Outcome measures

#### Primary outcome measures

The primary study outcomes will be depressive symptoms as measured by the CES-D.

#### Secondary outcome measures

Secondary outcomes will be self-management of diabetes, glycaemic control, diabetes-related distress and health-related quality of life measured as described previously.

#### Tertiary outcome measures

Tertiary outcomes will be biochemical markers reflecting common pathophysiological processes of insulin resistance, inflammation and oxidative damage that are assumed to be intertwined in both diabetes and depression.

### Data analysis

Continuous data will be summarized for each group using descriptive statistics. The distributions of continuous data at the follow-up assessments will be compared by the linear mixed-effects model the flexibility of which makes it the preferred choice for the analysis of repeated-measures data.

Categorical data will be summarized for each treatment group using counts and percentages. The distributions of categorical data in each treatment group will be compared using the Pearson Chi-square test.

In addition to the effects of intervention on psychological and biomedical outcome variables, data on participation rate among eligible individuals (intervention reach) will be considered relevant.

All analyses will be performed by StatSoft Statistica version 7.0.

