**Methods and Design:**

Type 2 diabetic patients aged 18-65 yrs. who report mood difficulties and the related need for help in a mail survey will be potential participants. After giving informed consent, they will be randomly assigned to one of the three groups (psychoeducation, physical activity, treatment as usual). Depressive symptoms, diabetes distress, health-related quality of life and diabetes self-care activities will be assessed at baseline, at 6 weeks, 6 months and 12 months. A structured clinical interview for DSM-IV Axis I Disorders (SCID-I) will be performed at baseline and at one-year follow-up in order to determine the clinical significance of the patients' depressive symptoms. Disease-related data will be collected from patients' files and from additional physical examinations and laboratory tests.

The two interventions will be comparable in terms of format (small group work), duration (six sessions) and approach (interactive learning; supporting the participants' active roles). The group treated as usual will be informed about their screening results and about the importance of treating depression. They will be provided with brief re-education on diabetes and written self-help instructions to cope with mood difficulties.

Primary outcomes will be depressive symptoms. Secondary outcomes will be glycaemic control, diabetes-related distress, self-management of diabetes and health-related quality of life. Tertiary outcomes will be biochemical markers reflecting common pathophysiological processes of insulin resistance, inflammation and oxidative damage that are assumed to be intertwined in both diabetes and depression. The mixed-effect linear model will be used to compare the outcome variables.

Power analysis has indicated that the two intervention groups and the control group should comprise 59 patients to enable detection of clinically meaningful differences in depressive symptoms with a power of 80% and alpha = 0.05. Outcomes will be analysed on an intention-to-treat basis.

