### Randomisation

This study design has three arms: psycho-educational intervention, physical activity intervention, and depression screening followed by diabetes treatment as usual. Eligible participants will be randomised into one of the three groups by using a computer-assisted approach. Groups will be balanced by age and sex. Randomisation will be carried out by a member of the team who will not take part in the treatment. Data on patients (SCID-I assessment, baseline and follow-up data) will be collected by team members unaware of the patients' group assignment. Baseline and one-year follow-up structured clinical interview (SCID-I) will be administered by the same person on both occasions.

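### Free improvement: the stated comparison of follow-up values gives baseline CES-D, age and sex no role in the model, and naming them would add precision at no cost

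*Protocol article*

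**What the plan says.** The Data analysis section of the protocol article covers every continuous outcome in one sentence: "The distributions of continuous data at the follow-up assessments will be compared by the linear mixed-effects model". It lists no fixed effects or covariates. The abstract adds only that a mixed model will be used for the outcome variables. The primary outcome falls under this sentence: "The primary study outcomes will be depressive symptoms as measured by the CES-D".

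Three other places bear on the point:

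- **Assessments.** Baseline (T0) is one of four time points, and "Psychological questionnaires will be applied at all points of measurement". A T0 value of the CES-D, PAID, SF-12 and SDSCA therefore exists for each patient, and HbA1c is on the same schedule.
- **Randomisation.** "Groups will be balanced by age and sex". The method of balancing is not described.
- **Assessments, closing paragraph.** Treatment preference is to be adjusted for. This is the only adjustment named in the article.

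The sample size appears in the abstract: "the two intervention groups and the control group should comprise 59 patients", "with a power of 80% and alpha = 0.05". No difference, standard deviation or correlation is given.

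**The concern.** The article treats baseline and follow-up as separate terms. Read literally, its analysis sentence describes a contrast among T1 to T3 values in which T0 is neither a covariate nor a response. Age and sex are built into the allocation but have no stated place in the analysis.

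Two things would be at stake if the trial were analysed as the sentence reads:

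- **Baseline.** Allocation is balanced on age and sex, not on CES-D. Stable between-patient differences in CES-D, which T0 could remove, would stay in the error term, and the contrasts would be less precise than the collected data allow.
- **Balancing factors.** Balanced allocation makes the true variance of the arm difference smaller. A model that ignores the balancing factors does not register this, so its standard errors come out too large.

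There is also a smaller benefit in settling the matter. The choice between an unadjusted, a change-score and a baseline-adjusted contrast for the primary outcome would be fixed before the data are seen.

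**Working it through.** **Inputs from the protocol article:** 59 patients, 80% power, alpha 0.05 (abstract); three arms balanced on age and sex (Randomisation); CES-D measured at T0 and at each follow-up (Assessments).

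**Assumptions, because the article gives no figure:** 59 is per group; the test is two-sided; the 59 refers to an unadjusted comparison of two arms at one visit; the baseline to follow-up correlation r is 0.3 to 0.7; age and sex explain a share R² of CES-D variance between 0.02 and 0.20.

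**Step 1. The plan's own figure.** The 59 cannot be reproduced, since no difference or standard deviation is stated. Solved backwards with the normal approximation:

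d = (1.960 + 0.842) × √(2/59) = 0.516

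If 59 were the total, about 20 per arm, the same formula gives d = 0.89. Steps 2 and 3 do not depend on which reading is right. In both, the expected z-value at the design difference is 1.960 + 0.842 = 2.80.

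**Step 2. Adding the baseline value.** The residual standard deviation is multiplied by √(1 − r²), so power = Φ(2.80/√(1 − r²) − 1.96). The number per arm that would give 80% power is 59(1 − r²), rounded up.

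| r (assumed) | Power with baseline | Per arm for 80% |
|---|---|---|
| 0 | 80.0% | 59 |
| 0.3 | 83.6% | 54 |
| 0.5 | 89.9% | 45 |
| 0.7 | 97.5% | 31 |

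The gain is about 4 to 18 percentage points.

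**Step 3. Age and sex, assuming allocation is well balanced on them.** The true variance of the arm difference is multiplied by (1 − R²), while the unadjusted model still estimates the full variance. The standard error is too large by the factor 1/√(1 − R²), and the actual type I error is 2 × [1 − Φ(1.96/√(1 − R²))].

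| R² (assumed) | SE too large by | Actual type I error | Power without / with age and sex |
|---|---|---|---|
| 0.02 | 1.0% | 4.8% | 80.2% / 80.8% |
| 0.05 | 2.6% | 4.4% | 80.6% / 82.0% |
| 0.10 | 5.4% | 3.9% | 81.3% / 84.0% |
| 0.20 | 11.8% | 2.8% | 82.7% / 87.9% |

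**Step 4. Does the gain persist with repeated measures?** Take the mean of the three follow-ups, d = 0.516 at 59 per arm, and a common correlation r between all visits. The variance factor is (1 + 2r)/3 without baseline and (1 + 2r)/3 − r² with it. Power goes from 97.0% to 98.8% (r = 0.3), from 92.9% to 99.1% (r = 0.5) and from 87.9% to 99.9% (r = 0.7). The direction is the same. The gain is smaller than in Step 2 because averaging over visits already adds precision.

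**The case against.** The strongest objection is that silence is being read as exclusion. The analysis sentence names a class of model and lists no terms at all, not even treatment arm. A condensed article commonly leaves the covariate list to the full protocol or the SAP, and neither is shown. The sentence may only say where the contrast is read. A model with T0 as covariate or response also compares arms at follow-up. The adjustment for treatment preference is stated in the Assessments section and not repeated under Data analysis, so absence from that section does not prove absence from the model. All of this stands. A reader might infer that the trial will leave out baseline CES-D, age and sex, but the article does not say so.

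A second objection concerns validity. A reader might infer that the planned error bars are wrong or that false positives are inflated. Neither follows. Without baseline CES-D, a randomised comparison has valid standard errors that already allow for chance imbalance; they are only wider. Only the balancing factors can miscalibrate them, by a small amount and in the conservative direction. Even that presumes good balance, and the method is not described.

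A third objection concerns size. The difference, r and R² are all assumed. Patients must report mood difficulties on the PHQ-2 and must not have current major depression. That narrows the baseline range and would tend to lower r. At r = 0.3 the gain is under 4 points. This also stands, and it is why the range is shown.

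What remains is that the sentence, followed as written, gives a less precise contrast than data already scheduled for collection would allow.

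**Conclusion.** This is a free improvement, not an error. The article describes a comparison of follow-up values, gives T0 no stated role, and does not carry the two allocation factors into the model.

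If the analysis were run that way, the main cost would be efficiency: about 4 to 18 points of power for r between 0.3 and 0.7 at a single visit. This rests on 80% being the unadjusted power at two-sided 0.05. The age and sex part is minor. At R² of 0.05 to 0.10 the standard errors are about 3% to 5% too large and the nominal 5% test runs at 4.4% to 3.9%.

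A reader might go further and conclude that the 59 is wrong or the trial underpowered. The documents do not support that. The 59 can be neither reproduced nor refuted without a difference and a standard deviation. Under the assumptions above, the unadjusted comparison keeps its planned 80%. The direction of the gain is certain for any non-zero correlation of useful size; its amount is not known.

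**What to change.** Add one sentence to the Data analysis section, for example: each continuous outcome is analysed by a linear mixed model on T1 to T3 with arm, visit, arm × visit, the baseline value of that outcome, baseline × visit, age and sex as fixed effects; the primary CES-D contrasts are read from this model. An acceptable alternative is a constrained model with T0 as a response and a common baseline mean across arms, plus age and sex.

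If the full protocol or the SAP already specifies such a model, it is enough to align the sentence with it.

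The cost is one sentence. All the terms are already collected or used in allocation, no new data are needed, and the sample size stays as it is.

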### Ethical aspects

The study protocol has been approved by the Vuk Vrhovac University Clinic's Ethics Committee. Patients will be provided with information about this trial, their rights and the data to be collected from them, and a written informed consent will be obtained from all participants.

## Abbreviations

HbA_1c_: glycated haemoglobin; PHQ-2: Patient Health Questionnaire; SCID-I: Structured Clinical Interview for the DSM-IV Axis I Disorders; GP: general practitioner; CES-D: Center for Epidemiologic Studies Depression Scale; PAID: Problem Areas in Diabetes; SF-12: Short Form Survey; SDSCA: Summary of Diabetes Self-Care Activities; BMI: body mass index; WHR: waist-to-hip ratio; WBC: white blood cell count; DNA: deoxyribonucleic acid; SMBG: self-monitoring blood glucose
